In summary, there is evidence that a dysregulated inflammatory response in patients with COVID-19 pneumonia may cause ARDS with unfavorable prognosis. Many of them will require mechanical ventilation for long time, overcrowding the regional health system. The treatments of the severe COVID-19 pneumonia in unknown and randomized trials are needed to test their efficacy. The steroids, as unspecific anti-inflammatory agents, may shorten the respiratory failure and improve the prognosis. Low-lose dexamethasone reduced the risk of death in patients with oxygen needs, or mechanical ventilation. The aim of this study is to explore the effectiveness and safety of high-dose dexamethasone, against usual care, in the treatment of SARS-CoV-2 pneumonia, in patients with ARDS.

MATERIALS AND METHODS

TRIAL DESIGN

Multicenter randomized clinical trial, controlled, open, parallel group, to evaluate the effectiveness and safety of high dose dexamethasone in adult patients with confirmed COVID-19, with Acute Respiratory Distress Syndrome.

MAIN OUTCOMES

The main result is ventilator-free days at 28 days (Days without ventilator support in the first 28 days following randomization).

Secondary outcomes measures

• 28-days mortality (Dead rate within 28 days of randomization)

• 90-days mortality (Dead rate within 28 days of randomization)

• Frequency of nosocomial infections (number of ventilator-associated pneumonia, blood stream infection or candidemia in the first 28 days following randomization)

• Viral shedding (Frequency of positive PCR on nasopharyngeal swab 28 days after randomization)

• Serum C - reactive protein variation (10 days after randomization)

• SOFA variation (over the first 10 days after randomization)

• Use of prone position (Cumulative hours spent on prone position at 10 days after randomization)

• Delirium (Frequency of delirium at ICU discharge)

• Muscle weakness (mMRC score at ICU discharge)

PARTICIPANTS

We will include patients with SARS-Cov-2 pneumonia who develop acute respiratory distress syndrome, in several intensive care units (ICU) in Buenos Aires, Argentina.

Inclusion criteria:

- Men and women, with age ≥ 18 years old.
- Diagnosed SARS-CoV-2 infection, by PCR.
- Diagnosis of Acute Respiratory Distress Syndrome (hypoxemic respiratory failure not explained by cardiac disease + PaO2/FiO2 ratio < 300 with a Positive End-Expiratory Pressure ≥ 5 cm H2O + bilateral pulmonary infiltrates)(23)

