- Cough during aspiration maneuvers

The trial will be performed in pressure support ventilation (pressure support 8-10 cm H_2_0, and ZEEP, with a FiO_2_ <= 50%), if possible. If the test is passes successfully, the attending physician will decide, or not, to extubate the patient. This test can be done daily.

POSSIBLE CONFOUNDERS

The following variables will be evaluated as possible confounders:

- Age and gender
- Ventilatory mode, and parameters of mechanical ventilation
- Oxygenation variables (pH, PaO_2_, PaCO_2_)
- Severity scores (APACHE II (28), SOFA (29))
- Shock
- Co morbidities (Charlson score (30))

RANDOMISATION AND BLINDING (MASKING)

Treatment will be assigned according to site stratified randomization by permuted random blocks sequence 1:1 generated with a table in R language. The randomization table is concealed in the randomization tool of the REDCap (Research Electronic Data CAPture) platform.

This is an open trial, so no masking of treatment assignment will be used.

SAMPLE SIZE

Assuming a 3 days difference in ventilator-free days between treatment groups, with a mean of 9 days, and a standard deviation of 9 days; the necessary sample size would be 284 subjects (142 per group), with a power of 80% and a two-tailed alpha error of 0.05.

STATISTICAL ANALYSIS:

All tests will be on an intention-to-treat basis. Initially, a descriptive analysis will be performed. The different variables will be compared according to the treatment with usual statistical test according to data distribution (normality of data will be evaluated by Shapiro-Wilk test).

Main outcome variable analysis (ventilator free-days) will be compared by Wilcoxon test. A competing risk model will be done for the time to first successful extubation, adjusting for APACHE II score and ARDS severity. Two competing events (successful weaning and dead under mechanical ventilation) will be evaluated; sub-hazard ratio will be calculated by the Fine and Gray method.

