Survival at 28 days will be evaluated by Cox regression analysis, with assigned treatment, APACHE II and ARDS severity as predictors. Change in different daily parameters (vital sign, SOFA score, chemistry, sedation, parameters of mechanical ventilation, among others) will be compared by a mixed-effect regression model (fixed and random), using the treatment as fixed variable and the patient code and the day of data acquisition as random. The same procedure will be performed for safety measures, using glucose levels and insulin requirements. Number of infections in the first 28 days will be analyzed with a Poisson model, with treatment, APACHE II score, and ARDS severity as predictors. A quasi-Poisson model, or a negative binomial, will be done in case of over-dispersion. In this case the results will be expressed to the best fit model, according to Akaike Information Criterion (AIC).

The analysis will be carried out with the statistical package R: A language and environment for statistical computing (R Core Team, R Foundation for Statistical Computing, Vienna, Austria. URL <http://www.R-project.org/>).

TRIAL REGISTRATION AND CURRENT STATUS

The trial was registered under the title “Dexamethasone for COVID-19 Related ARDS: a Multicenter, Randomized Clinical Trial” with ClinicalTrials number NCT04395105, registered on 20 May 2020. The protocol with code DEXA-ARDS-COVID19, version 3.0 on date: 13/MAY/2020 is already approved by the Local Research Ethics Committee of CEMIC. The trial is already in the recruitment phase.

ETHICS APPROVAL AND CONSENT TO PARTICIPATE

The protocol was evaluated by the Local Research Ethics Committee of CEMIC (Buenos Aires, Argentina), on May 13, 2020 with the reference code 1264. It was approved on May 13, 2020. The study was also approved by the SATI (Sociedad Argentina de Terapia Intensiva) Ethics Committee.

Patient’s next of kin will be asked for informed consent. This will be reflected in the medical record before included in the clinical trial. A copy of the informed consent will be attached in the medical record.

REFERENCES

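### The only effect measure named for time to extubation is the Fine-Gray sub-hazard ratio, which does not directly isolate the rate of weaning; adding cause-specific models is a cheap improvement

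*Protocol*

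**What the plan says.** The Statistical Analysis section of the protocol plans one model for time to extubation: "A competing risk model will be done for the time to first successful extubation, adjusting for APACHE II score and ARDS severity". It then fixes the events and the effect measure: "Two competing events (successful weaning and dead under mechanical ventilation) will be evaluated; sub-hazard ratio will be calculated by the Fine and Gray method".

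Three other statements bear on the point:

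- The primary endpoint, ventilator-free days, is defined under Main Outcomes as "Days without ventilator support in the first 28 days following randomization". The test is the Wilcoxon test ("Main outcome variable analysis (ventilator free-days) will be compared by Wilcoxon test"). The protocol does not say how deaths are scored.
- Mortality has its own model: "Survival at 28 days will be evaluated by Cox regression analysis", with treatment, APACHE II and ARDS severity as predictors.
- The summary that closes the background says that steroids "may shorten the respiratory failure and improve the prognosis". These are two different effects.

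**The concern.** A Fine-Gray model for weaning keeps patients who have died on the ventilator in the risk set, because it models the cumulative incidence of weaning. If treatment prevents some of these deaths, more patients live long enough to be weaned. The weaning sub-hazard ratio then rises above 1 even when the daily rate of weaning among ventilated patients is the same in both arms. The reverse also holds: faster weaning removes patients from the risk of dying on the ventilator and pulls the death sub-hazard ratio below 1.

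The rationale separates shorter respiratory failure from better prognosis. The named analyses give no estimate that belongs to the first effect alone. At stake is the interpretation of a secondary analysis: a ratio above 1 could be taken to show faster weaning when the cause was fewer deaths.

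**Working it through.** **The plan's own figure.** The Sample Size section assumes a 3-day difference ("Assuming a 3 days difference in ventilator-free days between treatment groups") and "a standard deviation of 9 days", with 80% power and two-sided alpha 0.05. Per arm, n = 2 × (1.960 + 0.842)² × 9² / 3² = 2 × 7.85 × 9 ≈ 141.3, so 142 per arm and 284 in total. This agrees with the protocol, and nothing below changes it.

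**Assumptions for the check.** The protocol gives no weaning or death rates for the trial. I assumed constant daily hazards w (weaning) and d (death on the ventilator), with complete follow-up to day 28. Fine-Gray is then the same as a Cox model that keeps patients with the competing event at risk to day 28. By day 28,

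share weaned = w/(w + d) × (1 − exp(−28(w + d))), and share dead on the ventilator = d/(w + d) × (1 − exp(−28(w + d))).

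**Hand check, w = 0.045 and d = 0.030.**

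- Control: 0.600 × (1 − exp(−2.100)) = 52.7% weaned; 0.400 × 0.878 = 35.1% dead.
- Death hazard × 0.65, weaning rate unchanged (d = 0.0195): 0.698 × (1 − exp(−1.806)) = 58.3% weaned.
- Weaning rate × 1.5, death hazard unchanged (w = 0.0675): 0.308 × (1 − exp(−2.730)) = 28.8% dead, down from 35.1%.

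So the share weaned rises with no change in the weaning rate, and the share dead falls with no change in the death hazard.

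**Fitted ratios (large-sample simulation).** Each cell gives the weaning sub-hazard ratio / the death sub-hazard ratio.

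| Control hazards w/d | Control weaned / dead | Death HR 0.65 only | Death HR 0.50 only | Weaning HR 1.5 only |
|---|---|---|---|---|
| 0.045/0.030 | 52.7% / 35.1% | 1.14 / 0.67 | 1.21 / 0.52 | 1.42 / 0.80 |
| 0.055/0.025 | 61.4% / 27.9% | 1.12 / 0.67 | 1.18 / 0.52 | 1.41 / 0.78 |
| 0.040/0.030 | 49.1% / 36.8% | 1.14 / 0.67 | 1.21 / 0.52 | 1.43 / 0.81 |

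Cause-specific Cox models on the same data recover 1.00 for the unaffected event in every row. Allowing for simulation error across separate runs, the ranges are about 1.12 to 1.22 (weaning, death effect only) and 0.77 to 0.82 (death, weaning effect only).

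**Second check, using mortality figures in the protocol's background.** These are used as death on the ventilator, which is an assumption. The share of controls weaned is assumed to be 40%, 50% or 55%, and the weaning hazard is equal in both arms.

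- Deaths 40.7% to 29.0% (ventilated patients in the large open-label dexamethasone trial): weaning sub-hazard ratio 1.14, 1.19, 1.21.
- Deaths 36% to 21% (the Spanish ARDS trial): 1.17, 1.21, 1.24.

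In the 40.7% to 29.0% case with 50% weaned, the ratio is 1.19, yet mean days ventilated within 28 days rise from 10.7 to 12.2, because patients who would have died stay on the ventilator. In the same control setting, a weaning hazard 10% lower combined with a death hazard ratio of 0.50 still gives a weaning ratio of 1.14.

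**Do the other analyses isolate weaning?**

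- *Ventilator-free days.* If deaths score 0 (an assumption), the mean in the same 40.7% to 29.0% case rises from 9.5 to 10.5 with no change in the weaning hazard.
- *28-day Cox model.* It concerns death. If nobody dies after extubation (an assumption), the hand check above shows that faster weaning alone lowers 28-day mortality from 35.1% to 28.8%.
- *Both sub-hazard ratios together.* The patterns differ: about (1.12 to 1.21, 0.52 to 0.67) for a pure death effect, against (1.41 to 1.43, 0.78 to 0.81) for a pure weaning effect. This helps, but neither number estimates the weaning rate.

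**The case against.** Several points on the other side stand.

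- **Fine-Gray is a legitimate choice.** It answers how treatment changes the cumulative chance of being weaned. The protocol nowhere says that the ratio will be read as weaning speed. A reader might infer that the plan would report a survival benefit as faster extubation, but the text does not say so.
- **A reader might infer that the model cannot show whether ventilation is shortened, or that the two ratios fail to separate the effects.** That is too strong. Both events are to be evaluated, survival has its own model, and the pairs of ratios look different under the two mechanisms. In a simulation at 142 per arm (first setting), among death-only trials (hazard ratio 0.65) with a significant weaning ratio, the death ratio was also significant in 90%. In weaning-only trials the corresponding figure was 29%.
- **A reader might infer an inflated false-positive rate.** In the second check, at 142 per arm and unadjusted, the Fine-Gray weaning test rejects in 12 to 27% of trials with equal weaning hazards, against 4 to 5% for cause-specific Cox. The share weaned really differs between arms there, so the higher figure is power against a true difference and not type I error.
- **This is not the only analysis bearing on ventilation.** The primary endpoint also does. The Fine-Gray model is the only one named for time to extubation.
- **An SAP that is not at hand may already add cause-specific models.** The point is therefore limited to the effect measure that the protocol itself fixes.

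What remains is that none of the named analyses directly estimates the rate of weaning, while the rationale treats shorter respiratory failure as an effect in its own right.

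**Conclusion.** The point holds as a cheap improvement to a supportive analysis, not as an error that invalidates the plan. The sub-hazard ratios are valid for cumulative incidence but do not isolate weaning speed. A pure effect on death (hazard ratio 0.65 to 0.50) moves the weaning ratio to about 1.12 to 1.22, and a pure effect on weaning (ratio 1.5) moves the death ratio to about 0.77 to 0.82. These sizes rest on constant hazards, assumed weaning and death rates, complete follow-up and unadjusted models, so they are illustrative; the direction does not depend on the particular rates chosen. Ventilator-free days may also combine death and ventilation, depending on how deaths are scored.

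**What to change.** Add two cause-specific Cox models, one for successful weaning and one for death on the ventilator, each adjusted for APACHE II and ARDS severity as already planned. Report their hazard ratios beside the two sub-hazard ratios and the cumulative incidence curves for both events. State before the data are analysed that any claim of faster weaning rests on the cause-specific ratio, and that the weaning sub-hazard ratio describes the share of patients weaned by day 28.

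The cost is two further fits on the same data. The downside is that four ratios are reported where two were planned, so the text must say which question each one answers. No new data are needed.

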The Surviving Sepsis Campaign COVID-19 panel supported a weak recommendation to use steroids in the sickest patients with ARDS due to SARS-CoV-2 (19). Cochrane could not issue a report on the benefits of steroids, due to the absence of evidence in patients with COVID-19, and asked for time until the results of ongoing trials (19). A recommendation against the general use of steroids in patients with COVID-19 was initially issued by the NIH (National Institute of Health), the WHO (World Health Organization), the CDC (Center for Disease Control), and the IDSA (Infectious Disease Society of America), due to the absence of clear evidence (20,21).

Recently, the RECOVERY trial provides evidence that treatment with dexamethasone at a dose of 6 mg once daily for up to 10 days reduces 28-day mortality in patients with Covid-19 who are receiving respiratory support (22). This British study compared multiple treatments for COVID-19 in a randomized, open label trial, with a complex design, in patients with different severities. This sub study randomized 6425 patients (ratio 1:2) to received dexamethasone 6 mg/day for ten days against placebo. A decreased in 28-days mortality (21.6% vs. 24.6%) was seen as main outcome (age-adjusted rate ratio 0.83; IC 95% 0.74 a 0.92; P<0.001). The benefit was greater in the more severe patients who needed oxygen (n=3883; 21.5% vs. 25.0%, rate ratio 0.80 IC 95% CI 0.70 a 0.92; p=0.002) or mechanical ventilation (n=1007; 29.0% vs. 40.7%, rate ratio 0.65 IC 95% 0.51 a 0.82; p<0.001). These results were presented before the publication, and several institutions, such as the NHS and the NIH, changed their recommendation in favour of the use of dexamethasone (6 mg qd for 10 days).

The preliminary results of the RECOVERY trial made us change our original design for the usual care. In the beginning, this study sought to compare dexamethasone (higher doses than RECOVERY trial) versus usual care, without steroids. This approach is unfeasible nowadays, thus we modified our initial design to allow low dose dexamethasone for 10 days as usual care treatment. However, the dose proposed by the British study might not be enough to suddenly reverse the inflammatory changes in patients with ARDS.

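### The 28-day survival model, and the extubation and infection models with it, adjust for APACHE II and ARDS severity but not for age, which the trial records and lists as a possible confounder

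*Protocol*

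**What the plan says.** The Statistical analysis section of the protocol names the covariates of three secondary models:

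- 28-day survival: "Survival at 28 days will be evaluated by Cox regression analysis, with assigned treatment, APACHE II and ARDS severity as predictors".
- Extubation: "A competing risk model will be done for the time to first successful extubation, adjusting for APACHE II score and ARDS severity", analysed by the Fine and Gray method.
- Infections: "Number of infections in the first 28 days will be analyzed with a Poisson model, with treatment, APACHE II score, and ARDS severity as predictors".

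The section Possible confounders gives a separate list, introduced by "The following variables will be evaluated as possible confounders". Its first entry is "Age and gender". It continues with "Ventilatory mode, and parameters of mechanical ventilation", blood gas variables, APACHE II and SOFA, shock and the Charlson score. It gives no measurement time, no model and no selection rule, and the Statistical analysis section does not mention it again. The primary outcome, ventilator-free days, is compared by an unadjusted Wilcoxon test.

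**The concern.** The protocol treats age as a possible confounder, and its background section quotes the mortality result that led to the redesign as "age-adjusted rate ratio 0.83". Yet its own mortality model has no age term. If age predicts death beyond what APACHE II and ARDS severity capture, leaving it out has two consequences. Any chance age imbalance among 284 patients, with randomisation stratified only by site, stays in the treatment estimate. The hazard ratio is also drawn towards 1, with some loss of power.

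There is a smaller, related ambiguity. The protocol has one fixed covariate set and one open list, and does not say how they relate. SOFA and ventilation parameters are on the list and also appear among the daily measures compared between arms: "Change in different daily parameters (vital sign, SOFA score, chemistry, sedation, parameters of mechanical ventilation, among others". The text does not say that only values from before randomisation may serve as covariates.

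**Working it through.** **1. The plan's own figure.** Inputs from the Sample size section: difference 3 days, SD 9 days, two-sided alpha 0.05, power 80%, 1:1 allocation.

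n per group = 2 × (1.960 + 0.842)² × 9² / 3² = 2 × 7.849 × 9 = 141.3, rounded up to 142, so 284 in total. This reproduces the stated figure (power at 142 per group: 80.2%). It rests on an unadjusted comparison of ventilator-free days, so the covariates of the secondary models do not enter it.

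**2. Cox simulation with and without age.** 600 runs per setting, 142 per group, follow-up censored at day 28.

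- From the protocol: the group sizes, and a hazard ratio of 0.65, which the background section quotes for ventilated patients in the cited trial.
- Assumed: daily hazard 0.0182 for an average control patient, so 28-day mortality is 1 − exp(−0.0182 × 28) = 39.9%, against 40.7% quoted for ventilated controls in the cited trial; log hazard ratio 0.4 per SD of APACHE II; correlation 0.4 between age and APACHE II; log hazard ratio of 0 to 0.7 per SD of age, given APACHE II. ARDS severity was left out.

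| Age log-HR per SD | HR without age | HR with age | Power without age | Power with age | Gain (points) |
|---|---|---|---|---|---|
| 0 | 0.638 | 0.637 | 60.2% | 60.3% | 0.1 |
| 0.3 | 0.653 | 0.647 | 56.7% | 57.8% | 1.1 |
| 0.5 | 0.659 | 0.645 | 57.0% | 59.0% | 2.0 |
| 0.7 | 0.674 | 0.646 | 54.3% | 61.7% | 7.4 |

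In the last row, ln(0.674) / ln(0.646) = 0.395 / 0.437 = 0.90, so the model without age recovers about 90% of the log hazard ratio.

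Under a true hazard ratio of 1, rejection rates were 3.5% to 5.3% without age and 3.0% to 5.8% with age. The Monte Carlo standard error is √(0.05 × 0.95 / 600) = 0.9 points. There is no sign of inflation either way.

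**3. A second simulation with other assumptions.** 2000 runs per setting, 284 patients, about 93 to 98 deaths, hazard ratio 0.65, correlation 0.35 between age and APACHE II. For age log hazard ratios of 0.35, 0.50 and 0.65 per SD, power was 51.9%, 49.0% and 48.6% with the planned covariates, and 53.0%, 53.1% and 55.0% with age added. The gains are 1.1, 4.1 and 6.4 points, in line with step 2.

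**4. The other two models.** Neither was simulated. A rate ratio from a log-link Poisson model is not expected to shrink when a covariate independent of treatment is left out, so any gain there would come through precision alone. The case for age in the Fine-Gray and Poisson models is consistency across the three.

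**The case against.** The strongest reply is that this is a question of efficiency, not validity. Randomisation protects the test of no effect, the models are secondary, the primary test is unadjusted, and APACHE II may already carry much of the age information. The gain was small except at the strongest assumed age effects. All of this stands and limits the weight of the point. It does not argue against adding a value that is already recorded.

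Several stronger readings are tempting, and the protocol does not support them.

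- *The plan adjusts for variables that treatment can change.* A reader might infer this from SOFA and ventilation parameters appearing both as possible confounders and as daily outcomes. A baseline value can be a covariate while later values are outcomes, and nothing says that later values will be adjusted for. A day-3 score carrying half the effect would shrink a 3-day gain to about 1.4 days, but no such adjustment is planned, and the halving is built into the assumption.
- *Covariates will be picked by their result.* Taking the smallest p-value among 12 adjusted rank regressions would raise a 5% test to about 13%. The protocol plans no such regressions, and its three models have their covariates fixed in the text.
- *Oxygenation is badly handled.* The text says ARDS severity and does not say that it is a category. FiO2 can be read as one of the listed ventilation parameters. In the second simulation, continuous PaO2/FiO2 on top of age added only 0.5 to 1.0 point of power.
- *The cited trial shows how much age matters.* Its quoted proportions give ln(1 − 0.216) / ln(1 − 0.246) = 0.86, against the quoted 0.83. That gap is small beside the quoted interval of 0.74 to 0.92, compares a back-calculated ratio with a reported one, and says nothing about age balance in this trial.

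Site, the only stratification factor, is also absent from the three models. That is a separate question.

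**Conclusion.** The point holds as a modest one. The three models leave out age, which the protocol itself lists as a possible confounder. For the Cox model the cost is about 0 to 7 percentage points of power and, at the strongest assumed age effect, a hazard ratio of 0.674 in place of 0.646. The size depends on the assumed effect of age beyond APACHE II and on assumed correlations of 0.35 to 0.4 between the two; the protocol gives neither. The loss is smaller where APACHE II already carries age. The omission does not make the mortality test invalid. The missing measurement time and the undefined use of the confounder list need clarifying, but they do not show that an improper adjustment is planned.

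**What to change.** In the Statistical analysis section, add age as a continuous variable to the covariates of the Cox model and, for consistency, of the Fine-Gray and Poisson models. Keep APACHE II and ARDS severity, and state that all covariates are values from before randomisation. In Possible confounders, state that the list serves baseline description or analyses labelled exploratory, and does not drive the choice of covariates.

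The cost is wording, one more parameter per model, and a hazard ratio that is conditional on age and must be reported as such. No new data are needed.

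### The mixed model for daily parameters aims to compare change, but its only fixed term is treatment, so on raw values it compares average level without using baseline

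*Protocol*

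**What the plan says.** Under Statistical Analysis, the protocol states the aim and the model in one sentence: "Change in different daily parameters (vital sign, SOFA score, chemistry, sedation, parameters of mechanical ventilation, among others) will be compared by a mixed-effect regression model", and then "using the treatment as fixed variable and the patient code and the day of data acquisition as random". The next sentence extends this to safety: "The same procedure will be performed for safety measures, using glucose levels and insulin requirements".

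The Secondary outcomes list includes "SOFA variation (over the first 10 days after randomization") and "Serum C - reactive protein variation (10 days after randomization"). The first is named in the mixed-model sentence. The second is not, and would be covered only as part of chemistry or the unnamed remainder.

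For the Cox and Poisson models in the same section, the protocol lists APACHE II and ARDS severity as further predictors. For the mixed model it lists treatment alone.

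**The concern.** The aim is a difference in change, but the stated model does not encode one if the response is the raw daily value. A random day term has mean zero and is shared by both arms, so it cannot carry an arm difference over time. What remains is one treatment coefficient, the difference in average level.

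Three consequences follow. An effect that grows over days is averaged with the early days, when it is small. A chance imbalance at baseline passes straight into the estimate. The baseline value, which would remove much of the between-patient variance, is not used.

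At stake are the SOFA analysis, the other daily parameters and the planned glucose and insulin comparison. A non-significant averaged coefficient may be read as no effect on organ failure or no glycaemic harm when the analysis was simply imprecise. Detail left to an analysis plan would be no finding. Here, however, the protocol itself says which terms are fixed and which are random.

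**Working it through.** **The plan's own figure.** The only size calculation is for the primary outcome: "Assuming a 3 days difference in ventilator-free days between treatment groups, with a mean of 9 days, and a standard deviation of 9 days", giving "284 subjects (142 per group), with a power of 80% and a two-tailed alpha error of 0.05". Check: n per arm = 2 × (1.960 + 0.842)² × 9² / 3² = 141.3, rounded up to 142, or 284 in total, with power 80.2%. It reproduces and does not depend on the mixed model.

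**What the stated model estimates.** As written, y(i,j) = b0 + b1·treatment(i) + u(i) + v(j) + e(i,j), with patient effect u and day effect v random. With complete, balanced data, b1 is the difference between arms in patient means over all days. No coefficient is a difference in change.

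**Assumptions for the size of the problem.** The protocol gives no variances for daily parameters. Assume 142 per arm (from the sample size), days 0 to 10, complete data, patient intercept SD 3 (variance 9), independent slope SD 0.25 per day (variance 0.0625) and residual SD 1.5 (variance 2.25). Power = Φ(z − 1.96) + Φ(−z − 1.96), with z = difference / √(2V/142). V is the per-patient variance of each summary:

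- Stated term, mean of days 0–10: 9 + 5² × 0.0625 + 2.25/11 = 10.767; SE 0.389.
- Mean change from baseline, days 1–10: 5.5² × 0.0625 + 2.25/10 + 2.25 = 4.366; SE 0.248.
- Baseline-adjusted mean, days 1–10: (9 + 5.5² × 0.0625 + 2.25/10) − 9²/(9 + 2.25) = 11.116 − 7.2 = 3.916; SE 0.235.
- Slope contrast: 0.0625 + 2.25/110 = 0.0830; SE 0.0342 (110 is the sum of squared centred days).

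**Results.**

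| Summary | Linear divergence to 1 point: difference, z, power | Immediate 1-point shift from day 1: difference, z, power |
|---|---|---|
| Stated term | 0.50, 1.28, 25% | 10/11 = 0.909, 2.33, 65% |
| Mean change from baseline | 0.55, 2.22, 60% | 1.00, 4.03, 98% |
| Baseline-adjusted mean | 0.55, 2.34, 65% | 1.00, 4.26, 99% |
| Slope contrast | 0.10 per day, 2.93, 83% | 5/110 = 0.0455 per day, 1.33, 26% (27% by simulation) |

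For a linear divergence to 1.5 points, the same formulas give 49%, 91%, 94% and 99%. Dropping day 0 from the stated term barely helps: variance 11.116, SE 0.396, z = 0.55/0.396 = 1.39, power 28%.

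**Early effect that fades.** Assume 1.5 units on days 1–5 and 0.3 on days 6–10. The stated term has difference 9/11 = 0.818, z = 2.10, power 56%. The baseline-adjusted mean has 0.9/0.235, z = 3.83, power 97%. A baseline-adjusted day-10 contrast has V = (9 + 100 × 0.0625 + 2.25) − 7.2 = 10.3, SE 0.381, z = 0.3/0.381 = 0.79, power 12%.

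**Separate simulation** (4,000 runs; assumed SDs 2.5, 0.3 and 1.5). When slopes differed by 0.1 per day but overall means were equal, the stated term rejected 5% of the time and a slope contrast 72%. When both arms changed identically but differed by a constant 1 point, the rates were 82% and 5%. The stated term responds to level, not to change.

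**The case against.** The strongest reply is that the sentence takes change in the daily parameters as its subject. If change from baseline is the response, the treatment term is the arm difference in mean change, which is a valid comparison. That stands as a possible reading: it loses some efficiency (60% against 65% with baseline adjustment) but is not wrong. The protocol does not say that this is the response, and what it lists are the daily parameters themselves.

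Second, a reader might infer that the stated model cannot test a treatment effect at all. The document does not support that. The averaged term picks up part of a divergence and has 65% power for an immediate shift under the same assumptions. The fault is dilution and wasted baseline information.

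Third, a reader might infer that a treatment-by-day slope is simply the right test. The ranking depends on the shape of the effect, which the protocol does not state, and for an immediate shift the slope contrast does worst.

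Fourth, it is tempting to say that glycaemic harm would be missed. No figure supports that. The planned dose in group 2 changes after the first 5 days, so a steadily growing glucose difference is not the obvious pattern, and a day-10 contrast could hide early harm.

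Two further inferences should not be pressed. Treating day as a random slope is possible, but two random intercepts is the more natural reading. CRP may be analysed as a two-point change by another test.

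**Conclusion.** The point holds as a mismatch between a stated aim and a stated model, limited to secondary and safety analyses. On raw values the planned coefficient is a difference in average level that ignores baseline. On a change-from-baseline response it is valid but somewhat inefficient, and the protocol does not say which applies.

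Baseline adjustment gains in all three shapes examined: 25% to 65% for linear divergence to 1 point, 65% to 99% for an immediate shift, and 56% to 97% for an early effect that fades. These figures rest on assumed variances and complete data to day 10. Death and discharge will make the data incomplete, so they show relative efficiency and do not predict the trial's power. CRP is affected only if it is analysed within this model. The Wilcoxon comparison of ventilator-free days and the sample size are untouched.

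**What to change.** Replace the mixed-model sentence with one to this effect:

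*Post-baseline daily values will be analysed by a linear mixed model with treatment, day (categorical), treatment by day and the baseline value as fixed effects, and patient as a random effect.*

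Then name the contrast for each outcome:

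- SOFA: the baseline-adjusted treatment difference over days 1–10, reported with the treatment-by-day test.
- Glucose and insulin: the baseline-adjusted difference averaged over the treatment days, plus the day-specific differences, not a day-10 contrast alone.
- CRP: state whether it belongs to this model or is a two-point comparison.

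The 83% above belongs to a single linear slope contrast. The categorical treatment-by-day test spreads over several degrees of freedom and should not be expected to match it for a linear divergence. If slopes vary between patients, a random slope for day alongside the patient intercept keeps the interaction test from understating its standard error.

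The cost is a sentence or two of text, a slightly more complex model and a few more parameters. The software is unchanged and no new data are needed, provided that a baseline value is recorded.
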